### Definition of Adverse Event

An AE is any untoward medical occurrence in a participant to whom Vi-TCV or IPV has been administered, including occurrences that are and are not caused by or related to the vaccine. All AEs related to study vaccination that are reported by telephone or by home or clinic visits in the first 7 days after vaccination will be recorded, including the event description, the date of onset, the resolution, the level of severity, an assessment of relatedness to the study, and the outcome.

### Seriousness of Event

An untoward medical occurrence that meets any one of the following criteria is considered serious: results in death; is life-threatening; requires inpatient hospitalization or a prolongation of an existing hospitalization; or results in a persistent or significant disability. Other important medical events may be considered serious if the event jeopardizes the participant or requires intervention to prevent 1 of the above consequences.

### Protocol Deviations

Protocol deviations will be collected in a CRF and kept in the study record. Deviations that affect the study’s scientific integrity or a volunteer’s rights/safety will be reported to the University of Maryland and local IRBs.

### Analysis

Study hypotheses and power analyses are found in Table 3. The intention-to-treat population includes all randomized individuals, in the vaccine groups to which they were assigned, and all follow-up time, beginning with the time of randomization. The primary analysis will be based on this population. The per-protocol population includes all vaccinated individuals, in the vaccine groups based on the vaccines they received. Additional details of study analyses will be included in a statistical analysis plan, which will be written by the study biostatistician before the study’s data analysis begins.

**Table 3. T3:** Study Hypotheses and Power Analyses.

	Hypothesis	Power Analysis
**Cohort 1:** Children 9–11 months of age (n = 100), enrolled in a double-blind, individually randomized, controlled trial. With an expected 10% dropout rate, we anticipate 90 children (90% of 100 enrolled) will complete follow-up assessments: 45 in Group 1 and 45 in Group 2.	Reactogenicity following Vi-TCV given together with YFV and MR (Group 1) is not significantly different from reactogenicity following IPV given together with YFV and MR (Group 2).	The expected incidence of any grade 2 or greater solicited, systemic adverse events over 7 days following vaccination is 10% in Group 2 [14]. Sample sizes of 45 in Group 1 and 45 in Group 2 achieve 80% power to detect a minimum difference of 0.23 (= 33% - 10%), using a 2-sided z-test with unpooled variance and a significance level of 5% (PASS 15).
	The percentage of participants with seroconversion (≥2-fold rise) in yellow fever neutralizing antibodies following a single dose of Vi-TCV given together with YFV and MR (Group 1) is not significantly different from the percentage of participants with seroconversion (≥2-fold rise) in yellow fever neutralizing antibodies following a single dose of IPV given together with YF and MR (Group 2).	In Group 2, the expected seroconversion proportion is 70% [14]. Sample sizes of 45 in Group 1 and 45 in Group 2 achieve 80% power to detect a minimum difference of 0.28 (= 70% - 42%), using a 2-sided z-test with unpooled variance and a significance level of 5% (PASS 15).
**Cohort 2:** Children 15–23 months of age (n = 150) will be randomized 1:1:1 to 1 of 3 treatment groups. With an expected 10% dropout rate, we anticipate 135 children (90% of 150 enrolled) will complete follow-up assessments: 45 in Group 3, 45 in Group 4, and 45 in Group 5.	Reactogenicity following a single dose of Vi-TCV given together with IPV and MR (Group 3) is not significantly different from reactogenicity following a single dose of Vi-TCV given together with MCV-A and MR (Group 4).	The expected incidence of any grade 2 or greater solicited, systemic adverse events over 7 days following vaccination is 10% in Group 3 [14]. Sample sizes of 45 in Group 3 and 45 in Group 4 achieve 80% power to detect a minimum difference of 0.23 (= 33% - 10%), using a 2-sided z-test with unpooled variance and a significance level of 5% (PASS 15).
	Reactogenicity following a single dose of Vi-TCV given together with MCV-A and MR (Group 4) is not significantly different from reactogenicity following a single dose of IPV given together with MCV-A and MR (Group 5).	The expected incidence of any grade 2 or greater solicited systemic adverse events over 7 days following vaccination is 10% in Group 5 [14]. Sample sizes of 45 in Group 4 and 45 in Group 5 achieve 80% power to detect a minimum difference of 0.23 (= 33% - 10%), using a 2-sided z-test with unpooled variance and a significance level of 5% (PASS 15).
	The percentage of participants with seroconversion (≥4-fold rise) in meningococcal A bactericidal antibodies following a single dose of Vi-TCV given together with MCV-A and MR (Group 4) is not significantly different from the percentage of participants with seroconversion (≥4-fold rise) in meningococcal A bactericidal antibodies following a single dose of IPV given together with MCV-A and MR (Group 5).	In Group 5, the expected seroconversion proportion is 90% [14]. Sample sizes of 45 in Group 4 and 45 in Group 5 achieve 80% power to detect a minimum difference of 0.23 (= 90% - 67%), using a 2-sided z-test with unpooled variance and a significance level of 5% (PASS 15).
	The percentage of participants with seroconversion (≥4-fold rise) in Anti-Vi IgG antibodies following a single dose of Vi-TCV given together with IPV and MR (Group 3) is not significantly different from the percentage of participants with seroconversion (≥4-fold rise) in Anti-Vi IgG antibodies following a single dose of Vi-TCV given together with MCV-A and MR (Group 4).	In Group 3, the expected seroconversion proportion is 95% [8]. Sample sizes of 45 in Group 3 and 45 in Group 4 achieve 80% power to detect a minimum difference of 0.20 (= 95% - 75%), using a 2-sided z-test with unpooled variance and a significance level of 5% (PASS 15).

Abbreviations: IgG, immunoglobulin G; IPV, inactivated poliovirus vaccine; MCV-A, meningococcal A conjugate vaccine; MR, measles-rubella vaccine; Vi-TCV, Vi-typhoid conjugate vaccine; YFV, yellow fever vaccine.

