## TRIAL OVERVIEW

A randomized, controlled, Phase II trial will test Vi-TCV co-administration with vaccinations routinely given at 9 and 15 months of age in Burkina Faso. Our aim is to assess the safety and immunogenicity of Vi-TCV when co-administered with vaccinations routinely given to children at both 9 and 15 months of age in Burkina Faso. The Vi-TCV vaccine or an inactivated poliovirus vaccine (IPV) will be administered. Children 9–11 months of age will be randomized 1:1 to Vi-TCV or IPV; children 15–23 months of age will be randomized 1:1:1 to Vi-TCV + MCV-A, Vi-TCV + IPV with delayed MCV-A, or MCV-A + IPV. We will use block randomization with varying block sizes from 6–12. Our study objectives and endpoints are listed in Table 1.

**Table 1. T1:** Primary, Secondary, and Exploratory Objectives and Endpoints

	Objectives	Endpoints
**Primary**	To assess the safety of Vi-TCV when co-administered with Expanded Program on Immunization vaccines among children 9–11 months of age and 15–23 months of age in Burkina Faso.	1. Proportion of participants who develop adverse events in the first 30 minutes after vaccination and for 7 days after vaccination. 2. Proportion of participants who experience SAEs within 6 months of vaccination, in all participants. 3. Proportion of participants who experience other, non-serious adverse events up to 28 days following vaccination.
**Secondary**	1. To assess the immunogenicity of YFV when given with and without Vi-TCV in children 9–11 months of age. 2. To assess the immunogenicity of MCV-A when given with and without Vi-TCV in children 15–23 months of age. 3. To assess the immunogenicity of Vi-TCV when given with YFV in children 9–11 months of age. 4. To assess the immunogenicity of Vi-TCV when given with and without MCV-A in children 15–23 months of age.	1. Immunogenicity of YFV: yellow fever plaque reduction neutralization test at Days 0 and 28 in infants 9–11 months of age. 2. Immunogenicity of MCV-A: serum bactericidal antibody assay against *Neisseria meningitidis* serogroup A at Days 0 and 28 in children 15–23 months of age. 3. Immunogenicity of Vi-TCV when given with YFV: anti-Vi IgG antibody titer, as measured by ELISA at Days 0 and 28 in infants 9–11 months of age. 4. Immunogenicity of Vi-TCV when given with and without MCV-A: anti-Vi IgG antibody titer, as measured by ELISA at Days 0 and 28 in infants 9–11 months of age.

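### The set labelled per-protocol is an as-treated safety set, and the primary safety analysis is fixed on children as randomized rather than as vaccinated

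*Protocol article*

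**What the plan says.** The Analysis section of the protocol article defines two populations. The first: "The intention-to-treat population includes all randomized individuals, in the vaccine groups to which they were assigned, and all follow-up time", counted from randomization. Of this set it says: "The primary analysis will be based on this population". The second: "The per-protocol population includes all vaccinated individuals, in the vaccine groups based on the vaccines they received". Further analysis details are deferred to a statistical analysis plan.

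Four other places bear on these definitions:

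- Table 1 (Trial Overview) gives one primary objective: "To assess the safety of Vi-TCV when co-administered with Expanded Program on Immunization vaccines among children 9–11 months of age" and among those aged 15–23 months. All three primary endpoints are proportions with events in a period after vaccination.
- Definition of Adverse Event: "An AE is any untoward medical occurrence in a participant to whom Vi-TCV or IPV has been administered".
- Protocol Deviations: "Protocol deviations will be collected in a CRF and kept in the study record". Some are also reported to the IRBs, but none is linked to an analysis population. Table 4 sets a Day 28 window of ±3 days, which is not linked to one either.
- Table 3 frames each hypothesis as an absence of significant difference. The first is that reactogenicity in Group 1 "is not significantly different from reactogenicity following IPV given together with YFV and MR (Group 2"). No margin is given.

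**The concern.** There are two separate problems, both in rules that the article states.

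**Label.** A per-protocol set normally contains children who received what they were assigned and can be evaluated. The set given that name here requires only vaccination. A child given the wrong study vaccine is counted as per-protocol in the other arm. A major deviation or an out-of-window Day 28 sample is no ground for exclusion. A reader of the results would take a per-protocol table as an adherence check on the non-interference comparisons (secondary objectives 1, 2 and 4), and it would not be one.

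**Choice of set for primary safety.** The endpoints and the adverse event definition presuppose vaccination, but the primary set is formed at randomization and grouped by assignment. A reaction to a wrongly given vaccine is charged to the other arm. A child who was randomized but never vaccinated belongs to the set, yet cannot have an adverse event under the article's definition.

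The direction matters because Table 3 hypothesises no difference. Dilution from misallocation favours that result, and for reactogenicity the worse error is to miss a true excess.

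**Working it through.** **Inputs.** Table 3: 45 evaluable children per group (50 enrolled, 10% dropout); grade 2 or greater solicited systemic events 10% v 33%; MCV-A seroconversion 90% v 67%; two-sided 5% z-test with unpooled variance; stated power 80%. Assumptions, because the article gives no such figures: a fraction m of each arm receives the other arm's vaccine at random; a fraction u of each arm is unvaccinated; a fraction v of children is non-evaluable.

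**Step 1: reproduce the plan's figure.**
- SE = √(0.10×0.90/45 + 0.33×0.67/45) = 0.0831.
- Power = Φ(0.23/0.0831 − 1.96) = Φ(0.81) = 79.0%, in line with the stated 80%.
- 45/(1 − 0.10) = 50 enrolled per group, which also agrees. The sample-size figures are not in question.

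**Step 2: swaps, analysed as randomized.** The observed rates are (1−m)×0.33 + m×0.10 and (1−m)×0.10 + m×0.33, so the difference is (1−2m)×0.23.

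| m | Difference as randomized | Power |
|---|---|---|
| 0 | 0.230 | 79.0% |
| 1% | 0.225 | 77.2% |
| 2% | 0.221 | 75.4% |
| 4% | 0.212 | 71.5% |
| 5% | 0.207 | 69.5% |

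At 50 per arm, 2% is one child in each arm.

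**Step 3: the same swaps, analysed as received.** Each child is counted under the vaccine given, so with random swaps the difference stays 0.23 and power 79.0% at every m.

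**Step 4: unvaccinated children, analysed as randomized.** If they are counted as event-free, the difference is (1−u)×0.23. At u = 5% this is 0.2185, with power 76.1%. The article does not state that counting rule, so this is only what would follow from it. The as-received set excludes these children.

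**Step 5: non-evaluable children kept in an immunogenicity comparison.** Take MCV-A seroconversion, with v = 5% counted as non-responders:
- both arms: 0.95×(0.90 − 0.67) = 0.2185, toward no difference;
- Vi-TCV arm only: 0.90 − 0.95×0.67 = 0.2635, away from no difference;
- Vi-TCV arm only, with true rates equal at 90%: 0.90 − 0.95×0.90 = 0.045, an apparent difference where none exists.

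Retaining such children therefore has no fixed direction of bias.

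**The case against.** The strongest reply has four parts.

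- **The effect is small.** The study vaccine under comparison is one Day 0 dose prepared and given by dedicated unblinded staff, and screening and enrollment may fall on the same day, so swaps and unvaccinated children should be few. At 2–4% swaps the bias is 0.9 to 1.8 percentage points, against a 95% half-width of about 16 points (1.96 × 0.0831 = 0.163). This stands, and it limits the size of the point.
- **As-randomized analysis keeps the protection of randomization, which as-received grouping gives up.** This also stands, and is why the as-randomized analysis should be kept as sensitivity.
- **Evaluability rules belong in the analysis plan.** This stands for the detail. It does not excuse the label: the article itself fixes what per-protocol means, and the definition does not fit the name. It also fixes the population for the primary analysis.
- **The as-received set is already planned, so only its name and rank are in dispute.** That is largely true for safety. It does not supply an adherence-based set for immunogenicity.

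A reader might go further and infer that both populations pull toward no difference and that neither guards against it. The documents do not support this. Grouping by vaccine received drops unvaccinated children and places mis-vaccinated children with the vaccine they received (Step 3), and the bias from retained deviators can run either way (Step 5).

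**Conclusion.** The point holds as one of definition and choice of population, with modest numerical consequences. The set called per-protocol is an as-treated set. The primary safety analysis rests on a set that does not match its own endpoints or the article's adverse event definition. As-randomized analysis can dilute a true reactogenicity difference toward the hypothesised result: with an assumed 2% of each arm swapped, 0.23 becomes 0.221 and power falls from about 79% to 75%. The size depends wholly on that assumed rate. The as-received set is free of this dilution under random swaps, but it gives no per-protocol check on the seroconversion comparisons.

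It might also be inferred that non-significant results in two populations would together establish non-interference. They would not: Table 3 gives no margin, and two non-significant tests without one do not show that a difference is small.

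**What to change.** In the Analysis section, carried into the analysis plan before data analysis begins:

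1. Rename the all-vaccinated, as-received set the safety population and use it for the primary safety endpoints. Keep the as-randomized analysis as a sensitivity analysis.
2. Define a per-protocol immunogenicity set: children who received the assigned Day 0 study and routine vaccines, have Day 0 and Day 28 (±3 days) sera available, and have no deviation likely to alter the response.
3. Report the Group 1 v 2 (yellow fever), 4 v 5 (MCV-A) and 3 v 4 (anti-Vi) seroconversion differences with confidence intervals, in both the as-randomized set with data and the per-protocol set. Readers can then judge the differences by their size and precision.

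The cost is a few sentences, one extra set of tables, and a few children excluded from the per-protocol set. Enrollment and procedures do not change.

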### Ethical Considerations

The study will be conducted in accordance with the principles of the Declaration of Helsinki and in accordance with the principles of good clinical practice. The protocol and informed consent will be submitted to the University of Maryland IRB, the Regulatory Authority of the Ministry of Health of Burkina Faso, and the Ethics Committee for Health Research in Burkina Faso for written approval. Reports will be provided to the University of Maryland IRB and other parties annually. To compensate for their time and travel related to study activities, the participant’s parent/guardian will receive $15 (7500 Franc Communauté Financière Africaine) for every scheduled clinic visit.

To protect participant confidentiality, study records will be stored in a locked office or in a password-protected, secure database. No information concerning the study or the data will be released to any unauthorized third party.

### Potential Risks of Vi-Typhoid Conjugate Vaccine

In clinical trials among Indian children [8], adverse reactions were predominantly minor and transient. Local reactions, such as injection site pain, erythema, and induration, usually resolved within 48 hours of vaccination. Fevers ≥38°C have been observed in approximately 1–4% of vaccinees [15]. A post-licensure study of Vi-TCV co-administration with a measles-rubella–containing vaccine was conducted, as was a Phase IV comparator study with the WHO pre-qualified Vi-polysaccharide vaccine. In both studies, no safety signals were reported and the Vi-TCV safety profile was comparable to the respective comparator. Post-marketing surveillance of Vi-TCV, based on approximately 3000 reports, has shown fever, pain, and swelling around the injection site to occur in 1–10% of vaccinees in any age group, with no SAEs reported [16]. The WHO’s Global Advisory Committee on Vaccine Safety review found no safety signal related to the vaccine [16].

### Potential Risks of Inactivated Poliovirus Vaccine

The most common reactions following the receipt of an IPV are local injection site reactions (eg, pain, erythema, and induration) and moderate, transient fever. Other rare reactions (less than 0.01% of vaccine recipients) include edema, lymphadenopathy, transient arthralgia and myalgia, convulsions, headaches, paresthesia, somnolence, irritability, and allergic reactions (urticarial, facial edema, or anaphylactic shock) [17].

### Data

Research records will be stored in a locked room and on a secure electronic database, in compliance with International Conference for Harmonisation E6. Only authorized personnel will have access to these data. Regulatory agencies may examine the records for quality assurance reviews, audits, and the evaluation of the study’s safety and progress. Safety and immunogenicity data will be recorded on paper CRFs for subsequent data entry or entered directly into an electronic database. Study-specific CRFs will be generated.

### Quality Control and Quality Assurance

The site developed a protocol-specific quality management plan in conjunction with the University of Maryland Center for Vaccine Development and Global Health Office of Regulatory Affairs and Quality Management. This plan details how data will be evaluated for protocol compliance, which documentation will be reviewed, and the methods for training staff.

### Monitoring

The sponsor’s team will visit the site before the study’s start to discuss the protocol and data collection procedures with site personnel. Before participant enrollment, required regulatory documents must be available. Subsequent study monitoring will be conducted according to the sponsor’s requirements. Study monitors will periodically review the progress and access all records necessary to ensure the ethical and safe study conduct and the integrity/validity of recorded data.

### Plans for Dissemination of Results

The principal investigator and sponsor investigator will oversee the collection, approvals, and dissemination of study data. All publications and presentations will be reviewed by each co-investigator before submission. In accordance with the Bill & Melinda Gates Foundation policy, all study-related publications will be open access. Authorship will comply with International Committee of Medical Journal Editors guidelines.

### Clinical Trial Coordination

An on-site study physician will manage the daily study activities, with visits twice weekly by a senior study physician. Local study teams will participate in weekly teleconferences with international investigators to discuss the study’s progress, challenges, and planning. International investigators make regular visits to the study sites approximately every other month to review the progress and assist in study coordination.

The study is anticipated to begin recruitment activities in late 2018.

## DISCUSSION

This randomized, controlled clinical trial among infants and young children in Ouagadougou, Burkina Faso, will be the first in West Africa to test the pre-qualified Typbar-TCV. The study will provide the first information on co-administration of this vaccine with YFV and MCV-A, as recommended by the WHO. The rationale for the 3 arms in the older children is that both MCV-A and TCV contain tetanus toxoid as the carrier protein: thus, our study design allows us to carefully assess reactogenicity when those vaccines are given alone or together, and evaluate any effect on the antibody responses that might occur with a shared carrier protein. Such a phenomenon was noted with *Haemophilus Influenzae* Type b vaccines [18] and is thought to occur due to interference by a common protein carrier with common immunogenic epitopes [19]. We did not include an assessment of measles and rubella antibody responses, since this has been previously tested and we have attempted to minimize blood collection volumes in these young children.

Malaria parasitemia is prevalent among young children in Burkina Faso. We will test for *P. falciparum* parasitemia at Day 0 to evaluate the potential effect on the immunogenicity of Typbar-TCV and of the other vaccines administered.

**Table 4. T4:** Trial Schedule of Events. Abbreviations: AE, adverse event; SAE, serious adverse event.

Study Visit Type	Recruitment	Screening	Eligibility, enrollment, vaccination	Follow up	Follow up	Follow up	Follow up	Early termination
Study Visit Number		V00	V01	V02	V03	V04	V05	
Study Time point			D0	D3	D7±1	D28±3	D180±7	
Study introduction, recruiting	X	X^a^	X^a^					
Obtain informed consent		X	X^a,b^					
Review eligibility criteria		X	X^a,c^					
Review medical history		X	X^a,c^	X^c^	X^c^	X^c^	X^c^	X^c^
Review concomitant meds		X	X^a,c^	X^c^	X^c^	X^c^	X^c^	X^c^
Review vaccination history		X	X^a,c^	X^c^	X^c^	X^c^		X^c^
Axillary temperature^d^		X	X^e^			X		X
Height and weight and Middle Upper Arm Circumference (MUAC)		X	X^e^				X	X
Targeted physical exam		X^˚^	X^a,c,e,˚^			X^c,˚^		X^c,˚^
Vaccination			X			X^f^		
30-min post-vaccination evaluation			X					
Post-vaccination reactogenicity assessment				X	X			X
Venous blood collection for immunogenicity			X^e,g^			Xg		X^g^
Venous blood collection for malaria parasitemia			X^e^					
Assess and record SAES			X^h^	X	X	X	X	X
Assess and record solicited AEs			X^h^	X	X			X^i^

^a^If not performed at previous visit.

^b^Confirm informed consent for study procedures.

^c^Review/confirm information or activity in participants previously consented and screened.

^d^Participants must not eat or drink anything hot or cold within 10 minutes before taking oral temperature.

^e^Prior to study vaccination and used as a baseline.

^˚^Targeted physical exam if indicated based on interim medical history.

^f^Only for children in Group 3 in the 15 through 23 month old cohort

^g^3-5m1 of blood collected for immunogenicity and noninterference testing ^h^If AE/SAE occurs post-vaccination

^i^Only if visit occurs within 7 days after study vaccination.
